## *Figure 2. Example of possible layout of hotspots (black blocks) and the surrounding areas (grey blocks) where hotspot targeted interventions will be evaluated). The depicted grid cells are 250x250m.*

## d. Intervention

Up to sixteen clusters will be defined as in the example shown in figure 2. Each cluster consists of a hotspot of malaria transmission and the area surrounding the hotspot 500m in each direction. In the entire study area current malaria control interventions will continue without interruption. In the intervention clusters (i.e. half of the identified hotspots), interventions will be superimposed on ongoing control measures: these intervention hotspots will be targeted with IRS, LLINs, larviciding and FSAT. All the intervention measures will be discussed in more detail in section f. ‘Procedures- Intervention Phase’ however, a brief overview is provided below.

*Indoor Residual Spraying (IRS)*

IRS will be carried out twice per year in all households in the intervention hotspots in the period preceding the long rainy season (March 2012) and six months later (September 2012). Meetings will be held with DOMC to discuss the optimal insecticide for use in the context of ongoing IRS activities in the district.

*Long Lasting Insecticide Treated Bednets (LLIN)*

All compounds in intervention hotspots will be visited in March 2012 and each house will receive a Long Lasting Insecticide Treated Nets for each sleeping space. The DOMC will be consulted about which type of LLINs should be distributed and how best to approach this, but activities will be undertaken by study personnel A follow-up visit is planned one month and 6 months after LLIN distribution to provide additional nets where needed and to monitor accurate use.

*Larviciding*

All mosquito larval habitats in all hotspots and evaluation zones will be mapped using handheld GPS systems in January. All habitats found to persist for more than a week within intervention areas will be treated with a larvicide that has been approved by the Pest Control Product Board and by DOMC, *Bacillus thuringiensis var. israelensis* (Bti) and/or *Bacillus sphaericus* (Bs). Larviciding will begin in March 2012 and continue weekly throughout the rainy season (until July 2012).

*Focal screen and treatment (FSAT)*

All compounds in hotspots will be visited in March 2012, and children between 6 months and 20 years of age will be tested for malaria parasites using a rapid diagnostic test based on the detection of malaria antigens (Premier Medical First Response Combo^®^,) using one of the best tests in a recent evaluation of the World Health Organization [18]. This test is based on the detection of *P. falciparum* specific histidine rich protein-2 (HRP-2) and Lactate dehydrogenase (LDH) and thereby circumvents problems of false-positivity common to HRP-2 based tests. If a single individual in this age group is found positive by RDT every individual within this compound will be treated with AL except for pregnant females. For these individuals transport will be provided to a health facility in the area and costs covered for examinations and government recommended anti-malarial treatments. Children under the age of 6 months will not be treated. A second round of FSAT is planned for September 2012.

Consent will be obtained separately for each intervention at the DOMC, administrative and community level (all interventions), the compound level (IRS and LLINs), or the individual level (FSAT). In the case of permanent breeding sites that are privately owned (e.g. fish ponds) verbal consent will be sought from community and owners before larviciding takes place. Other studies have shown no negative impact of larviciding using *Bacillus thuringiensis var. israelensis* on fish population and acceptance of larviciding by fish pond owners and the community ([name] *pers comm.*).

The other clusters will serve as control areas; hotspots in these areas will not be targeted.

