During a second visit, one month after initial LLIN distribution the correct usage of LLINs will be evaluated: the correct hanging of LLINs will be confirmed and household members will be asked to explain how they use the net. If needed, instructions about correct use will be repeated and additional nets can be provided if nets are missing or found to be torn. A third visit will occur to re-assess the quality and use of the nets 6 months after the first visit, in conjunction with the second round of IRS. At this point new ownership and quality will be re-assessed and new nets will be distributed as needed. All information on net use and quality will be recorded (appendix D).

*Focal Screening and Treatment (FSAT)*

Screening of a sentinel population within households

The FSAT utilizes individuals aged 6 month to 20 years as a sentinel group to indicate malaria exposure in the household because this age-group experiences the highest parasite burden [23-24]. For this age group all individuals will be tested for parasites using RDTs regardless of presence of symptoms or not. However clinical care will not be restricted to just this age group. All age groups may experience clinical malaria in our setting ([name] *et al.*, in preparation) and therefore those individuals over 20 years who are found to have fever will also be tested by RDT and receive treatment as oart of the FSAT intervention.

The FSAT campaign will take place in intervention hotspots in March 2012; a second round of FSAT is planned to take place in September 2012. Both campaigns will follow identical procedures.

Screening the sentinel group

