If no parasites are detected in the sentinel age group, it is unlikely that any parasite carriers are present in the household. If, on the other hand, one or more participant between 6 months and 20 years are parasite positive, it is likely that household members are also infected. Household members of malaria-infected individuals are up to 10-fold more likely to be infected with malaria themselves [2, 25][Mosha *et al.*, unpublished findings]. This household clustering of infections often occurs below the threshold density that allows infections to be detected by microscopy or RDTs. In other words, in households where somebody carries parasites as confirmed by RDT, there is highly significant clustering of low density infections that are negative by RDT and slide but positive by PCR [14, 25]. Up to 50% of all infections may be missed by RDTs or microscopy in settings like the Kenyan highlands because the density of infections is often very low [14]([name], in preparation). These asymptomatic low-density infections are clinically and epidemiologically relevant and can result in chronic anaemia and continued malaria transmission [35].

Treatment once parasites are detected in a household

We will give all people who reside in the same house as anyone (in the sentinel or non-sentinel group) found to be RDT positive a complete curative dose of antimalarials to clear parasite densities, except those under 6 months of age and pregnant women (see below), This focal treatment of parasite carriers in hotspots will maximize the impact of FSAT [26] since it includes symptomatic and asymptomatic, microscopic and submicroscopic parasite and gametocyte carriers. A proportion of those people who stay in the same house as parasite carriers will be themselves be free of detectable parasites at the moment of FSAT. Since there is currently no molecular assay that can detect these sub-microscopic infections in field settings, our approach is the only operationally feasible way to include microscopic and sub-microscopic parasite and gametocyte carriers without exposing individuals who are exposed to low malaria risk (i.e. those living outside hotspots of malaria transmission) unnecessarily to antimalarial drugs. In line with this, our approach should not be interpreted as mass drug administration since our treatment is restricted to small (<1km^2^) areas with proven high exposure to malaria.

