Pregnant women will not receive AL. Prior to consent and treatment, it will be explained why AL cannot be given to pregnant women and therefore the necessity to assess whether women of childbearing age may be pregnant if anyone in their household is found to be positive for malaria. Women may opt not to be tested for malaria. In each survey team there will be a female field worker trained to carry out interviews and test for pregnancy. She will approach women of childbearing age (13-45 years) in households where there is ≥1 parasite positive participant. These women will be asked whether they could be pregnant, and the date of their last menstrual period. Women whose last menstrual period was not within the prior 4 weeks, and/or who could be pregnant will be asked whether they would be willing to perform a pregnancy test on their urine sample. A recent survey of houses in the study area showed all to have pit latrines where a urine sample can be collected and a pregnancy test can then be conducted by the field worker away from the house. Women will be provided results of their pregnancy test in a private area in a confidential manner. This was shown to work in a sister study (SSC 1517). Confidentiality will be ensured at all times. Females whom have a negative pregnancy test can be given AL.

Women with a positive pregnancy test or those who would rather not have a pregnancy test performed will be offered a test for malaria parasites by RDT. If a woman who is pregnant or may be pregnant is parasite positive by RDT, she will be offered to be taken to a nearby health facility for examination and appropriate treatment before being returned home. If a women who is pregnant or may be pregnant is parasite negative by RDT, she will be asked about her last dose of intermittent preventive treatment in pregnancy (IPTp) with sulphadoxine-pyrimethamine (SP) and her antenatal records will be consulted. If the IPTp dose of SP was given <4 weeks ago, no additional treatment will be given. If the dose is >4 weeks ago or a woman has never received IPTp and the woman is eligible for a dose of SP according to national guidelines, she will be offered to be taken to a nearby health facility for examination and appropriate treatment before being returned home. All costs incurred by the woman will be covered by the project.

As part of the supervisory team a qualified Clinical Officer will be available to advise on all treatment regimes and any side effects from drugs taken.

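### Two treatment instructions conflict with the rest of the protocol: the survey form's OR literally offers treatment to some pregnant women, and FSAT is given two different treatment units

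*Protocol*

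**What the plan says.** **Survey form.** Appendix E, Part IV, carries a treatment rule directly under the RDT result. A positive person is offered treatment only if not pregnant OR, with the conjunction in bold capitals, without a malaria diagnosis and antimalarials in the previous 2 weeks.

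The body text on pregnancy is clear. Section 9f states "Pregnant women will not receive AL" and sets out a procedure: a question on the last menstrual period, an offered urine test and, where needed, referral. A woman who is or may be pregnant and "is parasite positive by RDT, she will be offered to be taken to a nearby health facility for examination and appropriate treatment". Section 12e says that pregnant women get alternative medication. Section 9g, which describes the surveys, has febrile RDT-positive people treated at home and refers back to the procedure for women of childbearing age. Section 12d names AL as the treatment for clinical malaria found in the survey.

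**FSAT unit.** The section 9d overview says that, once one person aged 6 months to 20 years is RDT positive, "every individual within this compound will be treated with AL except for pregnant females"; children under 6 months are also left untreated. Section 9f says: "We will give all people who reside in the same house as anyone (in the sentinel or non-sentinel group) found to be RDT positive" a curative course, again sparing infants under 6 months and pregnant women. Section 9f also brings in febrile adults: "those individuals over 20 years who are found to have fever will also be tested by RDT". Section 9d presents itself as a brief overview and adds: "All the intervention measures will be discussed in more detail in section f".

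**The concern.** Both places tell field staff whom to give a drug to. They are not background text.

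The form line is what a field worker has in view when an RDT turns positive during a survey. Followed word for word, it permits AL in a group that sections 9f and 12e exclude.

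For FSAT, the question is who receives AL when one person tests positive. The protocol keeps compound and house apart. In the net distribution, for example, "All compounds in intervention hotspots will be visited in March 2012 and each house will receive" nets by sleeping space. Section 9b speaks of the houses belonging to a compound, section 9g has teams visit each occupied house in a selected compound, and the Appendix C census sheet is headed by compound and lists people by house number. Without a single unit, the FSAT component cannot be described or reproduced exactly.

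The unit also bears on safety. The pregnancy assessment is tied to a positive result nearby: "She will approach women of childbearing age (13-45 years) in households where there is ≥1 parasite positive participant". If one team treated by compound while assessing pregnancy by house, women in the compound's other houses could be offered AL without that assessment.

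**Working it through.** There is no stated figure to reproduce. The check is a truth table for the form and a side-by-side reading for FSAT.

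**1. Form rule.** Take an RDT-positive person. Let P = pregnant and R = diagnosed and treated in the past 2 weeks. As printed, the rule is (not P) OR (not R). The alternative is (not P) AND (not R).

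| P | R | OR, as printed | AND | Body text |
|---|---|---|---|---|
| no | no | offer | offer | treat (9g, 12d) |
| no | yes | offer | do not offer | treat if febrile (9g, 12d) |
| yes | no | offer | do not offer | no AL; pregnancy procedure (9f, 12e) |
| yes | yes | do not offer | do not offer | no AL (9f, 12e) |

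OR offers treatment in 3 of 4 combinations, AND in 1 of 4. The two extra combinations are not equally wrong. The pregnant woman not recently treated is a direct conflict with sections 9f and 12e. For the non-pregnant person recently treated, the printed rule agrees with sections 9g and 12d, which treat febrile positives without a recent-treatment exception. So one combination contradicts the body text, and a bare AND would create a new gap in another.

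**2. Can the form correct itself?** The pointer to the pregnancy procedure is in section 9g, not on the form. As printed, Appendix E asks about drugs taken in the last 2 weeks (Part III) but has no pregnancy question.

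**3. FSAT, by case.** Take a compound of more than one house with the positive person in house A.

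| Positive person | Section 9d overview | Section 9f procedure |
|---|---|---|
| Aged 6 months to 20 years | everyone in the compound | everyone in house A |
| Only a febrile adult over 20 | silent | everyone in house A |

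The first row is a contradiction: the overview is wider. The second is an omission, which a brief overview may contain. The units coincide only where a compound has a single house.

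**4. Do other sections settle the unit?** Sections 9f (pregnancy) and 12c use the word household. The protocol uses it loosely. The background counts about 3,200 households in the baseline survey where section 9b counts 3,200 compounds. Consent for spraying and nets is at compound level in section 9d and at household level in section 9f. Those two mentions therefore cannot be counted for house or for compound. One statement stands on each side, with section 9d deferring to section 9f for detail.

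**5. Size.** The protocol gives neither the number of houses per compound nor the number of febrile, RDT-positive pregnant women expected in the surveys. Neither conflict can be turned into a count of people.

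**The case against.** The case for leaving the text alone is a fair one. Pregnant women are excluded from AL in sections 9d, 9f and 12e, with a full procedure, and section 9g points survey staff to it. The form line is phrased as a restriction and would naturally be taken to bar both groups; harm would need trained staff to read it as formal logic and disregard the rest. On FSAT, an overview that announces itself as brief and defers to section 9f is not a rival instruction.

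Most of this stands, and it limits the point. A reader might infer that the protocol means to treat pregnant women, or that FSAT itself admits them. The documents support neither: the body text is explicit, and the faulty line belongs to the cross-sectional survey. A reader might also count both extra truth-table combinations as errors, but treating a febrile, recently treated, non-pregnant person is what sections 9g and 12d say.

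What does not fall away is that the form is the instruction at the point of care, and it carries the wrong conjunction and no pointer. Nor does an overview's brevity explain naming a different treated unit: leaving detail out is one thing, stating a wider group is another. Section 9d promises more detail in section 9f but does not say which text prevails.

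**Conclusion.** Both conflicts are in the current text and should be corrected. The form, read literally, wrongly admits one of four combinations, the RDT-positive pregnant woman not recently treated. This is a wording error with a safety implication, already limited by the body text. The FSAT unit is stated two ways, compound and same house; section 9f probably governs, with any RDT-positive person as the trigger.

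Two further inferences would go too far. The mentions of households do not make the tally favour house. The documents also support no range for houses per compound, so the extra number treated under the overview cannot be bounded from them. The pregnancy-assessment gap in FSAT arises only if a team treats by compound and reads household as house. No effect on power, error rates, the primary analysis or a known number of people is claimed.

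**What to change.** **Appendix E, Part IV.** Replace the rule with wording such as: *RDT positive: offer AL only to a person who is not pregnant AND who has had no malaria diagnosis with antimalarial treatment in the past 2 weeks. Women who are or may be pregnant: follow the section 9f procedure. Febrile and treated in the past 2 weeks: refer to the clinical officer or a health facility.* The last sentence is needed because AND alone would leave a febrile positive person without care, against the intent of sections 9g and 12d.

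**Section 9d, FSAT.** Align unit and trigger with section 9f: treat everyone in the house of any RDT-positive person, whether in the sentinel age group or a febrile adult over 20, except pregnant women and children under 6 months. If the compound is what the sponsor wants, confirm that and change section 9f instead.

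**Sections 9f (pregnancy) and 12c.** Use the confirmed unit in place of household, so that the pregnancy assessment covers everyone who may be offered AL.

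The cost is one changed word and two added sentences on the form, plus wording edits in three places, before the first survey and FSAT round planned for March 2012. Design, sample size and analysis are unchanged.

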**Routine malaria control efforts in eight control clusters**

Any currently planned distributions of LLINs and yearly rounds of IRS will continue in the rest of the area. No interventions will be withheld from the population but no hotspot-targeted interventions will take place in the control clusters.

## d. Outcomes

*Primary outcome:*

1. The prevalence of *Plasmodium falciparum* parasitaemia as assessed by community surveys and measured by microscopy, RDT and PCR in hotspots of malaria transmission and in areas surrounding these hotspots.

*Secondary outcomes:*

1. The prevalence and density of serological markers of malaria exposure, antibodies against malaria-specific antigens, in hotspots of malaria transmission and in areas surrounding these hotspots.

## e. Sampling strategy and sample size calculation

The hotspot-targeted intervention will be evaluated inside and outside hotspots of malaria transmission. The latter is the main outcome measure of interest and forms the basis of sample size calculations. All available malaria simulation models indicate that malaria transmission in the area surrounding intervention hotspots would be considerably decreased because malaria transmission is effectively reduced/interrupted in those compounds that seed transmission to a larger geographical area [7-8, 19]. Because there are no published studies on the impact of hotspot targeted interventions, we determined the predicted impact of targeted interventions in our study area by one of the leading individual-based simulation model [19] using human, entomological and parasitological characteristics collected at our sites in Kenya. A previous study on the community benefits of insecticide treated nets in Asembo Bay, western Kenya, indicated that an indirect beneficial effect on malaria transmission may be limited to 500m from the intervention area [20]. We used this finding to define our evaluation zone surrounding the hotspots.

| [figure not shown] |
| --- |

***Figure 3. The predicted impact of untargeted and targeted interventions predicted by an individual-based simulation model.*** *Plotted are smoothed lines, the actual model estimates allow for seasonality.*

We modelled three scenarios in situations with a pre-intervention parasite prevalence in the human population of 5-15%: i) indoor residual spraying (IRS) in an untargeted approach, reaching 20% of the total population (black top line); ii) effective coverage with long lasting insecticide treated nets (LLINs) in an untargeted approach, reaching 80% of the total population (middle dashed grey line); iii) targeted IRS and 95% effective coverage with LLINs in the hotspots (bottom light grey line). The impact of larviciding is currently insufficiently parameterized to be included in the model [19].

We assumed a conservative estimate of the efficacy in detecting hotspots (75%, compared to 93% in Tanzania [[3](#_ENREF_3)]). Our simulations showed that targeted interventions can interrupt transmission completely, both inside and outside hotspots of malaria transmission, reducing overall parasite prevalence from 15% to <0.1%, in a manner that appears sustainable in the following years (see figure 3).

Our primary outcome of interest is the impact of hotspot-targeted interventions on parasite prevalence in the area surrounding the hotspot (the evaluation zone). If we evaluate our intervention in 300 randomly selected individuals living outside the hotspot per cluster and assume a conservative estimate of k (0.5 coefficient of variation of true proportions between clusters within each group), we need 8 clusters per arm to detect a reduction from 10% parasite prevalence at baseline to ≤ 5% after the intervention. The actual number of people sampled will depend on the size of the hotspot and surrounding evaluation zone, with a target of sampling 20% of the population in the evaluation zone (≤500m from edge hotspot) or a minimum of 100 and maximum of 500 people. The unit of randomization will be at the compound level therefore 100 people would equate to approximately 35 compounds.

We aim to evaluate the interventions in all age groups above 6 months. If the PCR results of the intensive survey indicates that parasite prevalence is below 10% in certain age groups, these age groups will be considered less suitable for evaluation purposes; they will receive the standard of care provided by the study, including screening and treatment of all febrile cases, but will not be routinely sampled.

To understand possible effect differences between clusters, we also want to determine whether our intervention succeeded in reducing malaria transmission inside hotspots. The estimated parasite prevalence in individuals between 6 months and 20 years of age who are living in hotspots is >20% ([name] *et al.*, unpublished data). With a sample size of 100 individuals per cluster (i.e. per hotspot in 16 clusters), we would be able to detect a reduction to ≤ 5% after the intervention (k=0.5; Z_α/2_=1.96; Z_β_=0.84). Again the actual number sampled will depend on the size of the hotspot, with a target of sampling 20% or a minimum of 50 individuals (approximately 9 compounds).

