## c. Definition of clusters for interventions

## The data collected during the intensive cross-sectional surveys (SSC 1802) will be used to detect hotspots of malaria transmission in the study area based on malaria parasite prevalence and antibody responses. Hotspots will be defined as areas that are smaller than 1km^2^ with a level of transmission intensity that exceeds that in the surrounding area (in all directions). This will be indicated by a statistically significant higher parasite prevalence in combination with a statistically significant higher SCR and/or age-adjusted density of antibodies malaria antigens.

Malaria parasite prevalence will be determined by PCR-based detection of parasites based on the *P. falciparum* mitochondrial cytochrome b gene [15].

Malaria specific antibody responses will be quantified as the age-dependent seroconversion rate (SCR) for antibodies against malaria: antigens apical membrane antigen-1 (AMA-1), merozoite surface protein-1 (MSP-1_19_) and glutamate-rich protein (GLURP) [[12](#_ENREF_12)]. Antibody responses will be measured by standard ELISA methodology [12, 16] and the SCR will be determined by fitting a simple model to the age-dependent prevalence of antibody responses, as described in detail in publicly available protocols [16]. In addition, age-adjusted antibody densities will be calculated [17]. The SCR will be estimated for geographical subsets of 50 observations.

Hotspots will be of variable size and no quantitative estimate of the elevated transmission intensity inside hotspots can be given a-priori since this depends on the transmission intensity of the surrounding area [2-3,16]. Clusters will include hotspots and a surrounding ‘evaluation zone’ of 500m from the edge of the hotspot (see figure 2); this forms the unit of randomization. The grid structure that divided the study area into 250x250m cells, created as part of the baseline cross-sectional study will be used as easy references for the areas defined as hotspots. The size of a hotspot or intervention area will not be defined by the maximum mosquito dispersal range. We are not aiming to identify independent niches of malaria transmission. Minimum distance between hotspots will be 1km. Mosquito dispersal outside hotspots of malaria transmission is essential for the community effect and forms the cornerstone of our evaluation.

[figure not shown]

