## g. Procedures: evaluation phase

**Community cross-sectional surveys**

*Consent procedure cross-sectional surveys:*

As with the intervention phase, meetings will be organised with the district commissioner, officers and chiefs with the district health team to seek approval for the evaluation phase. Sensitization of communities will be done by chiefs and assistant chiefs and village elders from the study area. Community meetings (barazas) will be held in the selected areas and study staff will explain the purpose of the surveys, the procedures to be followed and the risks and benefits of participation. Information sheets shall be provided in English, DhoLuo, or Kiswahili to all district representatives, chiefs and households (Appendix A).

Households will be informed at the barazas of the timing of the survey and that their compounds may be visited.

On the day of the cross-sectional survey informed consent will be obtained at the individual level. All consent forms will be available in English, DhoLuo, or Kiswahili. Translations will be checked through back-translation (Appendix B). Consent will be obtained by signature or thumb-print accompanied by the signature of an independent witness of selected individuals and/or their parents/guardians. Assent forms will be signed by children between the ages of 13 and 17 years and by their parents/guardians. Each assent form will be accompanied by consent form signed by the parent/guardian.

*Timing of the cross-sectional surveys:*

Six cross-sectional surveys will be conducted (see table in section 11):

- Pre-transmission season (March 2012)
- Peak transmission season (June 2012)
- Post transmission season (September 2012)
- Pre-transmission season (March 2013)
- Peak transmission season (June 2013)
- Post transmission season (September 2013; final survey)

*Procedure cross-sectional surveys:*

Prior to the surveys, census lists for all hotspots will be updated using PDAs, recording the name, age and gender of each household occupant (see appendix C for summary of information collected). For each cross-sectional survey up to 100 individuals above the age of 6 months will be randomly selected from malaria hotspots and up to 500 participants above the age of 6 months will be randomly selected from outside malaria hotspots in each cluster. Randomization will occur at the compound level.

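### The sample sizes count independent individuals, but the surveys select compounds; a compound design effect is missing, and its effect on planned power is modest

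*Protocol*

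**What the plan says.** Section 9e sizes the evaluation-zone comparison as follows: "If we evaluate our intervention in 300 randomly selected individuals living outside the hotspot per cluster", with the further instruction to "assume a conservative estimate of k (0.5 coefficient of variation of true proportions between clusters within each group", leads to the statement that "we need 8 clusters per arm to detect a reduction from 10% parasite prevalence at baseline to ≤ 5% after the intervention". The hotspot calculation uses 100 individuals per hotspot, a fall from over 20% to 5% or less, and "k=0.5; Z_α/2_=1.96; Z_β_=0.84". Neither calculation has a term for compounds.

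The same section then says: "The unit of randomization will be at the compound level therefore 100 people would equate to approximately 35 compounds". It equates the 50-person hotspot minimum with about 9 compounds. Section 9g, on the survey procedure, repeats: "Randomization will occur at the compound level". Field teams visit every occupied house in the selected compounds.

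Section 9c says of the hotspot together with its evaluation zone that "this forms the unit of randomization", and section 9f allocates clusters to the arms.

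Section 9f also gives the premise for focal screening and treatment: "Household members of malaria-infected individuals are up to 10-fold more likely to be infected with malaria themselves". It adds that infections detectable only by PCR cluster in households with a positive rapid test. PCR is the primary measure in section 10b.

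**The concern.** In the cluster-trial formula with k, within-cluster sampling variance enters as p(1−p)/n. That term is right only if the n people are independent draws from the cluster. When several people come from each selected compound and infections cluster within compounds, the variance is larger by a design effect 1+(m−1)·ICC, where m is the number sampled per compound.

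The coefficient k cannot absorb this. The protocol defines it as variation in true proportions between clusters, whereas the missing piece is sampling error within a cluster. The stated detectable reductions therefore credit each cluster with more information than the survey yields. The loss matters most at the permitted minimum samples (100 per zone, 50 per hotspot), where the within-cluster term is largest.

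**Working it through.** **Inputs from section 9e.** Zone: p0=0.10, p1=0.05, n=300 (permitted 100 to 500), k=0.5. Hotspot: p0=0.20, p1=0.05, n=100 (minimum 50), k=0.5. The z-values 1.96 and 0.84 are written for the hotspot and assumed to hold for the zone. People per compound: 100/35 = 2.86 in the zone, 50/9 = 5.56 in the hotspot.

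**Assumed ICC: 0.2 to 0.45.** The documents give none. As a rough guide, a risk ratio r between members of infected and uninfected households implies ICC = (r−1)p/(pr+1−p). At p=0.10, r=10 gives 0.9/1.9 = 0.47 and r=3 gives 0.2/1.2 = 0.17.

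**Formula.** Let V = DEFF·[p0(1−p0)+p1(1−p1)]/n + k²(p0²+p1²). Clusters per arm: c = 1 + (1.96+0.84)²·V/(p0−p1)², with (1.96+0.84)² = 7.84. Power at 8 per arm is taken from the noncentral t with 14 degrees of freedom and noncentrality (p0−p1)/√(V/8).

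**The plan's figure first (DEFF=1).**
- Zone: V = 0.1375/300 + 0.25×0.0125 = 0.000458 + 0.003125 = 0.003583, so c = 1 + 7.84×0.003583/0.0025 = 12.2. The stated 8 does not reproduce at k=0.5; power at 8 is 59%. That is a separate problem. Eight would follow from k of about 0.38 (0.377), which is not a protocol value.
- Hotspot: V = 0.2075/100 + 0.25×0.0425 = 0.002075 + 0.010625 = 0.0127, so c = 1 + 7.84×0.0127/0.0225 = 5.4. Eight per arm is enough (power 94%).

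The sampling term is only 0.000458/0.003583 = 13% of V in the zone and 0.002075/0.0127 = 16% in the hotspot, which limits what any design effect can do.

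**Design effects.**
- Zone: 1+1.86×0.2 = 1.37 to 1+1.86×0.45 = 1.84. Effective n is 300/1.37 = 219 to 300/1.84 = 163.
- Hotspot: 1+4.56×0.2 = 1.91 to 1+4.56×0.45 = 3.05. Effective n is 100/1.91 = 52 to 100/3.05 = 33.

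**Results with 8 clusters per arm.**

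| Setting | No compound effect: c, power | With compound effect: c, power |
|---|---|---|
| Zone, n=300, k=0.5 | 12.2, 59% | 12.8–13.4, 57–55% (ICC 0.2–0.45) |
| Zone, n=300, k=0.377 | 8.0, 79% | 8.5–9.2, 76–73% (ICC 0.2–0.45) |
| Hotspot, n=100, k=0.5 | 5.4, 94% | 6.1–6.9, 90–86% (ICC 0.2–0.45) |
| Hotspot, n=50, k=0.5 | 6.1, 90% | 8.1–9.1, 79–73% (ICC 0.3–0.45) |

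At the 50-person minimum with ICC 0.2, 7.5 clusters are needed, so 8 still suffices.

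**The case against.** Several objections carry weight.

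- **Size.** At the protocol's own k the between-cluster term dominates, so zone power moves by only a few points. This stands. A reader might put the value of 300 people as low as about 98, by applying a design effect of about 3 to the zone. That uses the hotspot's 5.56 people per compound; for the zone the protocol implies 2.86, and the value does not fall below about 163 for an ICC up to 0.45.
- **The ICC is assumed.** The 10-fold figure is an upper bound for households, and part of it may reflect differences between high- and low-transmission areas, which k already covers. This stands; only a range can be shown.
- **Larger samples are allowed.** A zone with 500 people and a design effect of 1.84 has an effective n of about 272, close to 300. This stands, but the actual number depends on zone size and may also be 100.
- **Hotspot shortfall.** A reader might infer that the hotspot objective is underpowered. The documents do not support that at 100 people. The shortfall needs every hotspot at 50 people and an ICC of about 0.3 or more. If the minimum binds because 20% of residents is fewer than 50, at least a fifth of the hotspot is sampled. Shrinking the within-cluster term by a fifth then gives 7.4 clusters (83% power) at ICC 0.3 and 8.2 (78%) at 0.45.
- **Whole compounds.** Section 9g also speaks of each selected participant, so full enumeration of a compound is an inference. The loss remains whenever several people per compound are taken.
- **Wording.** A reader might infer that compounds are randomised to arms. Sections 9c and 9f rule that out: clusters are allocated. The phrase in section 9e means random selection for the survey.

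**Conclusion.** The calculation is wrong as written but the consequence is small. The binomial terms for both strata omit the compound design effect, so 300 and 100 people overstate the information per cluster. Under the assumed ICC of 0.2 to 0.45, the cost in the zone at k=0.5 is about 2 to 4 percentage points of power, or 0.5 to 1.2 clusters per arm (12.2 to 12.8–13.4). Hotspots at 100 people are adequately covered by 8 per arm; the 50-person minimum is marginal at the upper part of the range.

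The compound effect does not explain why 8 clusters fails to reproduce at k=0.5; that gap exists without it. Nor does it threaten the analysis. Section 10b compares cluster-level prevalences using observed between-cluster variance, which already carries compound-level sampling error. This is a minor planning correction.

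**What to change.** In section 9e, multiply the p(1−p)/n terms by 1+(m−1)·ICC, stating m for zone and hotspot separately. Estimate the ICC within clusters from the 3,200-compound survey once its PCR results are available; section 9e treats them as pending, so until then give a stated range. Restate the power or detectable reduction for 8 clusters per arm at 300 and 100 people per zone and at 100 and 50 per hotspot. No clusters need be added on this account.

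As a wording correction only, change the unit of randomization in section 9e to *unit of survey sampling*, leaving the cluster as the unit allocated to arms.

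The cost is a short recalculation, an ICC estimate from a survey already carried out, and a slightly less favourable power statement. Conduct and analysis do not change.
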